## Methods/Design

### Design

This study is designed as a randomized controlled clinical trial with three study arms. The cost-effectiveness of two intensive one-year treatments that vary in inpatient period length and usual care for severely obese children and adolescents will be evaluated. There is a one year follow-up after treatment. Participants who meet the inclusion criteria and consent to participate in the study will be randomized to one of the three study arms (described under 'interventions'). Because of the nature of the treatments evaluated in this study, parents and participants as well as professionals at Heideheuvel and in the usual care condition cannot be blinded to the type of intervention. A table of random numbers is used to randomize participants. At the beginning of the first year 40 (13-18 years) participants are randomized into: group A (10), group B (10) or group C (20). The participants in group C will be randomized into group A (10) or B (10) after one year of receiving usual care. This process is repeated for another 40 participants (8-13 years) after 6 months. At the end of the fourth year all 80 participants (40 in each inpatient treatment group) will have completed the program and 1 year of follow up (Figure 1). Data collection started in August 2009 and will continue until July 2013. The Medical Ethics committee (METc) of VU University Medical Centre approved the study design, protocol and informed consent procedures.

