### Measurements

Primary outcome measure is (SDS) BMI. Secondary outcomes are quality of life and cardiovascular risk factors like blood pressure, bodily circumferences, serum lipids, glucose levels and insulin levels. Eating behavior and physical activity are also assessed. The EuroQoL (EQ-5D) is used to measure quality of life and to calculate Quality Adjusted Life Years (QALYs) over the follow-up period of 24 months. Measurements will be done at four points in time: at baseline (start of treatment) and after 6, 12 and 24 months.

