### Quality of life

Quality of life is measured using the EQ-5D [23]. The EQ-5D questionnaire contains a descriptive system of health related quality of life consisting of five dimensions (mobility, self-care, usual activities, pain/discomfort, and anxiety/depression). For each dimension there are three levels of severity (no problems/some or moderate problems/extreme problems). A standard vertical 20 cm visual analogue scale is also included to measure an individual's direct valuation of their current health-related quality of life state. Utilities will be estimated using the Dutch tariff [24]. Quality Adjusted Life Years (QALYs) will be calculated by multiplying the utilities with the amount of time a participant spent in a particular health state. Transitions between health states will be linearly interpolated.

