### Statistical analyses

An intention-to-treat analysis will be performed. A per protocol analysis will also be performed after careful description of correlates of non-adherence and dropout.

To take into account the repeated measurements over time, we will use generalized estimating equations for panel data analysis, also known as cross-sectional time-series analysis, with the use of the Stata software XTGEE command; this will allow us to account for the non-independence of repeated measurements of the same bio-indicator in the same participant over time. Linear regression will be applied for continuous outcomes and logistic regression for dichotomous outcomes. We will use age, sex, time point, and intervention group as explanatory variables in our models.

An economic evaluation from a societal perspective will be conducted alongside the randomized controlled trial. Multiple imputation will be used to impute missing cost and effect data. Five imputed data sets will be created, each of which will be analyzed separately. The results of these five analyses will be pooled using Rubin's rules [27].

Costs generally have a highly skewed distribution. Therefore, bootstrapping with 5000 replications will be used to estimate "approximate bootstrap confidence" (ABC) intervals around cost differences [28,29]. Incremental cost-effectiveness and cost-utility ratios will be calculated by dividing the difference in total costs between the groups by the difference in SDS-BMI and QALYs, respectively. Non-parametric bootstrapping will also be used to estimate the uncertainty surrounding the incremental cost-effectiveness and cost-utility ratios (5000 replications). The bootstrapped cost-effect pairs will be plotted on a cost-effectiveness plane (CE plane) [30] and used to estimate cost-effectiveness acceptability curves (CEA curves). CEA curves show the probability that the intervention is cost-effective in comparison with usual care for a range of ceiling ratios. The ceiling ratio is defined as the amount of money society is willing to pay to gain one unit of effect [31].

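### The incremental QALY and SDS-BMI differences are defined without adjustment for their baseline values, which costs precision in the ratios, the cost-effectiveness plane and the acceptability curves

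*Protocol article*

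**What the plan says.** All references are to the protocol article.

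- **Ratios (Statistical analyses).** The cost-effectiveness and cost-utility ratios are "calculated by dividing the difference in total costs between the groups by the difference in SDS-BMI and QALYs, respectively". A non-parametric bootstrap with 5000 replications supplies their uncertainty. The bootstrapped pairs feed both the cost-effectiveness plane and the acceptability curves. Missing costs and effects are multiply imputed (five data sets) and pooled by Rubin's rules.
- **Covariates (Statistical analyses).** The one covariate list stands with the GEE models: "We will use age, sex, time point, and intervention group as explanatory variables in our models". It contains age but no baseline outcome value.
- **QALYs (Quality of life).** QALYs are "calculated by multiplying the utilities with the amount of time a participant spent in a particular health state", and "Transitions between health states will be linearly interpolated".
- **Visits (Measurements).** Data are collected "at baseline (start of treatment) and after 6, 12 and 24 months".
- **Allocation (Design).** Forty adolescents are split into A 10, B 10 and C 20. Then "This process is repeated for another 40 participants (8-13 years) after 6 months". After one year of usual care, each cohort's group C is split 10/10 between A and B, which gives 40 in each inpatient group.

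**The concern.** With linear interpolation from the start of treatment, baseline utility is arithmetically part of each participant's QALY total, and later utilities will usually correlate with it. A chance difference in baseline EQ-5D between arms is therefore counted as QALYs gained or lost unless it is adjusted for. Baseline SDS-BMI acts in the same way on follow-up SDS-BMI if final values are compared.

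Cost-effectiveness is the stated objective. The Background section says that B was developed to match A's effect at lower cost, so the A-B QALY difference in the denominator is expected to be near zero. There, avoidable noise in the effect difference matters most: it spreads the points on the plane across quadrants and flattens the acceptability curves.

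**Working it through.** **The plan's own figure.** The only effect-size calculation is in Sample size calculation: 40 per group, difference 0.5 SDS-BMI, α 0.05, power 0.8, with no SD given. Solving backwards (two-sided, normal approximation): SD = 0.5 × √(40/2) / (1.960 + 0.842) = 0.798. An SD of 0.79 returns 40 per group and 0.80 returns 41 (power 0.798 at 40). The stated number can thus be neither confirmed nor refuted. The 0.798 is used below only as an illustration.

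**Assumptions not in the documents.** EQ-5D utility SD s = 0.15 to 0.25 (central 0.20); equal correlation r between any two visits, 0.3 to 0.7 (central 0.5). The small loss from estimating the regression slope is ignored.

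**A v B, two years, 40 v 40.** Trapezoid weights at 0, 6, 12 and 24 months are 0.25, 0.50, 0.75 and 0.50 (sum 2.0; sum of squares 1.125).

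- Var(QALY)/s² = 1.125 + (2.0² − 1.125)r = 1.125 + 2.875r
- Slope of QALY on baseline utility = 0.25 + 1.75r
- Share of variance removed by adjustment, R² = slope² / (Var/s²)

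| r | Var/s² | slope | R² |
|---|---|---|---|
| 0.3 | 1.9875 | 0.775 | 0.30 |
| 0.5 | 2.5625 | 1.125 | 0.49 |
| 0.7 | 3.1375 | 1.475 | 0.69 |

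At s = 0.20 and r = 0.5:

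- SE of the baseline difference = 0.20 × √(2/40) = 0.0447. Resulting shift in the QALY difference = 0.0447 × 1.125 = **0.050**.
- Unadjusted SE = 0.20 × √2.5625 × √(2/40) = **0.072**. Adjusted SE = 0.072 × √(1 − 0.494) = **0.051**.

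Over the assumed ranges, the one-SE shift runs from 0.15 × 0.2236 × 0.775 = 0.026 to 0.25 × 0.2236 × 1.475 = 0.082. The 95% range (× 1.96) is ±0.05 to ±0.16.

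**A or B v usual care, one year, 20 v 40.** Group C has only one year before re-randomisation, so the weights are 0.25, 0.50 and 0.25 (sum 1.0; sum of squares 0.375).

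- Var/s² = 0.375 + 0.625r, and slope = 0.25 + 0.75r. At r = 0.5 these are 0.6875 and 0.625, so R² = 0.57.
- SE of the baseline difference = 0.20 × √(1/20 + 1/40) = 0.0548. Shift = 0.0548 × 0.625 = **0.034**.
- Unadjusted SE = 0.0548 × √0.6875 = **0.045**. Adjusted SE = 0.0454 × √(1 − 0.568) = **0.030**.
- Over the assumed ranges, the one-SE shift runs from 0.15 × 0.2739 × 0.475 = 0.020 to 0.25 × 0.2739 × 0.775 = 0.053.

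**SDS-BMI, 40 v 40, SD 0.798.** SE for final values = 0.798 × √(2/40) = 0.178. A change score multiplies this by √(2(1 − r)); baseline adjustment multiplies it by √(1 − r²).

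| r | final value | change score | adjusted |
|---|---|---|---|
| 0.5 | 0.178 | 0.178 | 0.155 |
| 0.7 | 0.178 | 0.138 | 0.127 |
| 0.9 | 0.178 | 0.080 | 0.078 |

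At r = 0.7, adjustment cuts the SE by about 29% against final values (1 − 0.714), but by only about 8% against change scores (1 − 0.714/0.775).

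**The case against.** The quoted sentence is the general definition of an incremental ratio and is compatible with adjusted differences. The article nowhere calls the differences raw or unadjusted, and a condensed article may leave regression covariates to an analysis plan. This stands as a limit on wording: a reader might infer that the plan commits to raw differences, but the text does not say so. It does not dispose of the point. The article sets out the economic analysis in some detail, and carrying over its only covariate list would still leave out baseline utility.

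Other stronger readings also fail.

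- **Bias.** A reader might infer that the ratios are biased. They are not on this account. Chance imbalance is random error under randomisation, and a participant-level bootstrap already includes it. That a chance gap could decide the sign is true of any sampling error around a small difference; adjustment reduces that error.
- **Age cohort and randomisation round.** A reader might infer that imbalance in these enters the ratios. The fixed 10/10/20 allocation in each cohort and the later 10/10 split balance them by design. Omitting them can only cost precision.
- **SDS-BMI.** A reader might infer that a baseline gap passes straight through. The article does not say whether a final value, a change or a model estimate is used, and with a change score little is lost. This does not rescue the QALY area.
- **Usual care.** The article describes the acceptability curves as comparisons with usual care. The two-year figures do not apply to that one-year comparison, which has its own, smaller figures above.

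**Conclusion.** The point holds as one of efficiency. The plan names no adjustment for baseline EQ-5D or baseline SDS-BMI in the incremental effects, although baseline utility is a component of the QALY. The unadjusted analysis would be valid but noisier than it need be: the realised QALY difference moves with the chance baseline gap, the scatter on the plane is wider and the acceptability curves are flatter than the data require.

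The size rests on assumed EQ-5D SDs and correlations. Adjustment would remove about 30% to 69% of the variance of the two-year A-B QALY difference for r = 0.3 to 0.7, and about 57% of that of the one-year comparison with usual care at r = 0.5. The benefit for SDS-BMI depends on an unstated choice of final value or change score. The change is worth making because the baseline values are collected anyway.

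**What to change.** State in the analysis plan that, within each imputed data set and each bootstrap replicate:

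1. the incremental QALY is the arm coefficient from a regression on arm and baseline EQ-5D utility;
2. the incremental SDS-BMI is the arm coefficient from a regression on arm and baseline SDS-BMI;
3. age cohort and, where it applies, randomisation round (first allocation or re-randomisation after usual care) are added as covariates for precision;
4. these adjusted effects, paired with the cost difference from the same replicate, are used for the ratios, the plane and the acceptability curves.

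Keep the unadjusted ratio as a sensitivity analysis. Use the article's own definition of baseline (start of treatment) throughout, so that the covariate means the same for every participant. Resampling within arm is enough. Resampling within arm by cohort by round is not required: with cells of 10, an ordinary bootstrap understates the variance by a factor of 9/10, an SE about 5% too small (√0.9 = 0.95).

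The cost is a few lines in the plan and the code, with no new measurements and no extra participants.

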Group A will participate in a 6 months intensive inpatient treatment program during weekdays, followed by six monthly return visits of 2 days. Group B will participate in a 2 month intensive inpatient treatment program during weekdays, followed by biweekly return visits of 2 days during the next four months, then followed by six monthly return visits of 2 days. During the inpatient treatment phase and the 2-day return visits all children and adolescents stay overnight at Heideheuvel. Parents of participants in groups A and B will attend 1 session every week during the inpatient period and after that 1 session per return visit of their child. Group C will receive usual care during one year, after which the participants will be randomly allocated to the groups A and B. This implies that during this year they remain under the care of their pediatrician and other health care professionals that might be involved in their treatment like the general practitioner, dietician, physiotherapist and psychologist.

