### Cost measures

Cost calculations will be based on actual resource use, using prospective data collection during 2 years (the 12 months intervention period and the 12 months follow-up) through cost diaries. The costs of the interventions (inpatient care and recurrent return visits of 2 days) will be estimated using a bottom-up approach. Other costs include direct healthcare costs (e.g. costs of visits to the general practitioner, internist, physiotherapist, inpatient period), direct non-healthcare costs (informal care provided by parents and legal guardians and travel costs), and indirect costs (costs related to loss of productivity of the parents and legal guardians). Cost diaries are formatted as calendars on which health care utilization can be registered. The calendars will be sent to the families every 3 months. After 3 months the calendars will be returned by the parents, using stamped envelopes, also if there has been no health care utilization during that period. In case a calendar is not returned, use of health care will be inventoried by telephone calls and/or e-mails.

If available, standard costs recommended by the Dutch Health Insurance Council will be used to value resource use [25]. Medication costs will be valued using prices of the Royal Dutch Society of Pharmacy [26].

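### Usual care ends at month 12 for all of group C, so the plan's 24-month economic horizon cannot apply to the comparison with usual care

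*Protocol article*

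**What the plan says.** **Comparator.** The objective at the end of the Background asks for the cost-effectiveness of the two programmes against each other and against usual care, and the Discussion repeats this. Statistical analyses explains the acceptability curves with usual care as the reference: "CEA curves show the probability that the intervention is cost-effective in comparison with usual care for a range of ceiling ratios".

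**Horizon.** Under Measurements, the EQ-5D is used "to calculate Quality Adjusted Life Years (QALYs) over the follow-up period of 24 months". Under Cost measures, resource use comes from "prospective data collection during 2 years (the 12 months intervention period and the 12 months follow-up) through cost diaries". The Discussion also describes the short-term cost-effectiveness analysis as covering two years. No other horizon is given for any comparison.

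**Design.** Interventions states: "Group C will receive usual care during one year, after which the participants will be randomly allocated to the groups A and B". Design gives the numbers for an age cohort: "The participants in group C will be randomized into group A (10) or B (10) after one year of receiving usual care". A second cohort follows: "This process is repeated for another 40 participants (8-13 years) after 6 months".

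**Analysis rule.** Statistical analyses specifies intention-to-treat. It forms the cost-effectiveness and cost-utility ratios from between-group differences in total costs, SDS-BMI and QALYs, and applies multiple imputation to missing cost and effect data. It does not say how group C is handled after the switch.

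**The concern.** The stated horizon and the stated comparator do not fit together under this design. Every control participant enters one of the evaluated programmes halfway through the 24 months. If the economic analysis is run over 24 months by first allocation, the comparator's second year contains the intervention itself.

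Cost-effectiveness against usual care is one of the two comparisons in the objective. An analyst working from the article would have to choose the horizon and the starting point for group C, possibly with data in hand, and the choices answer different questions. A 24-month result labelled as a comparison with usual care would be a comparison with delayed treatment.

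**Working it through.** **1. Head-count (Design).** First allocation per age cohort is A 10, B 10, C 20. With two cohorts:

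- A: 10 + 10 = 20
- B: 10 + 10 = 20
- C: 20 + 20 = 40

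At month 12 each cohort moves 10 + 10 = 20 of its 20 group C participants into A or B. On usual care after month 12: 40 − 2 × (10 + 10) = 0. Planned usual-care person-months are 40 × 12 = 480 in months 0 to 12, and 0 in months 12 to 24. Final programme groups are A 20 + 20 = 40 and B 20 + 20 = 40.

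**2. Timeline from first randomisation.**

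| Months | First allocated to A or B | First allocated to C |
|---|---|---|
| 0–12 | programme | usual care |
| 12–24 | follow-up | programme A or B |
| 24–36 | – | follow-up |

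The randomised contrast with usual care exists in the first row only, which is 12 of the 24 months.

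**3. What a 24-month cost difference by first allocation would contain.** Let P_A and P_B be mean total cost in a programme year, F_A the mean cost in the year after programme A, and U1 and U2 the mean cost of a first and second year of usual care. Assume that all of group C start a programme, half in each, that programme-year cost does not depend on when it starts, and ignore discounting.

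- A versus two years of usual care: P_A + F_A − U1 − U2
- A versus C as designed: P_A + F_A − U1 − (P_A + P_B)/2 = (P_A − P_B)/2 + F_A − U1
- Gap between the two: (P_A + P_B)/2 − U2

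The same gap arises for B. A full average programme year is thus subtracted from the cost difference where a second year of usual care should be. The article gives no unit costs, so the gap cannot be put in money. QALYs and SDS-BMI at 24 months are affected in the same way, because group C has by then completed a programme.

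**4. Other ways to count 24 months.** Measurements places baseline at the start of treatment. If group C's clock starts when it enters a programme, its 24 months hold one programme year and one follow-up year, and no usual care. Multiple imputation does not help either. No participant has an observed second year of usual care, so imputed values would rest wholly on an assumption that the data cannot test.

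**5. What remains estimable.** Measurements are planned at 6 and 12 months, so A versus C (20 versus 40) and B versus C (20 versus 40) can be compared to month 12. A versus B can be compared over 24 months from start of programme (40 versus 40).

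**6. Precision, for context only.** The sample-size section gives 40 per intervention group for a 0.5 SDS-BMI difference between A and B, without an SD. Solving backwards (two-sided α 0.05, power 0.8): SD = 0.5 / [(1.96 + 0.84) × √(2/40)] ≈ 0.80. So 40 is attainable but cannot be confirmed, and it is not disputed here. For 20 versus 40 at the same difference, power = Φ(0.5 / [SD × √(1/20 + 1/40)] − 1.96). This gives about 0.63 at an assumed SD of 0.80, with a range from 0.86 (SD 0.60) to 0.45 (SD 1.0).

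**The case against.** The strongest reply is that no single sentence commits the plan to a 24-month comparison with usual care. The acceptability-curve sentence carries no horizon and reads as an explanation of the method. The 24 months come from Measurements, Cost measures and the Discussion, and Cost measures ties the two years to the intervention period plus its follow-up. A sympathetic reader could take A versus B as the 24-month comparison and usual care as the 12-month one. An article may also leave the horizon of each contrast to the full plan, and the flow chart (Figure 1), not reproduced in the text reviewed, may show group C's timeline.

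Part of this stands: the conflict comes from combining sections. But it is more than missing detail. The article gives one horizon for QALYs and costs, names usual care as a comparator for the ratios built on them, and describes a design in which the two cannot both hold. No flow chart can supply usual care that the text ends at month 12.

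Four stronger readings are tempting and are not supported:

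- **That the comparison with usual care is lost.** It is not; the 12-month version is randomised and estimable. The 24-month analysis by first allocation is also a legitimate estimate, but of immediate versus delayed treatment.
- **That 24 months of A or B would be set against 12 months of C**, creating a false gain of up to one QALY. The article nowhere proposes this.
- **That A versus B is excluded from the acceptability curves.** The ratios are defined between the groups, and A versus B is in the objective. One explanatory sentence does not exclude it.
- **That diaries and EQ-5D miss group C's usual-care year.** Calendars go to the families every three months and group C is not excepted. This is silence in a condensed article.

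**Conclusion.** The concern holds for the 24-month comparison with usual care only. From month 12, 0 of 40 control participants are on usual care, so a 24-month cost-effectiveness or cost-utility result by first allocation does not answer the stated question. Under the assumptions in the working, the cost difference would be off by the average programme-year cost less one year of usual care, an amount that the article does not allow to be put in money.

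The head-count rests on the planned numbers and on the re-randomisation going ahead as described. Drop-out before month 12 would reduce the number moving into A or B, but would not create usual-care data under the plan for the second year. Because usual care is a stated comparator in the objective, the horizon should be fixed before the economic analysis is run.

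**What to change.** In Statistical analyses, state two sets of comparisons:

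1. **Against usual care:** A versus C and B versus C by first allocation (planned 20, 20 and 40), with costs, QALYs and SDS-BMI over 12 months from first randomisation. State that group C's measurements and diaries are counted from that date.
2. **A versus B:** costs, QALYs, cost-effectiveness plane and acceptability curve over 24 months from start of programme (planned 40 versus 40). The analysis should account for whether a participant entered at the first or the second randomisation.

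Bring Measurements, Cost measures and the Discussion into line, and limit two-year conclusions to A versus B. If a 24-month contrast by first allocation is also wanted, label it as immediate versus delayed treatment.

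The cost is rewording. The downside is a shorter horizon against usual care, which the design already imposes. The modest precision of 20 versus 40 is likewise a consequence of the allocation, not of this change.
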